## Abstract

**Background::**

Cancer-related fatigue and its associated symptoms of sleep disorder and depression are prevalent in cancer survivors especially among breast, lung, and colorectal cancer survivors. While there is no gold standard for treating cancer-related fatigue currently, studies of mind-body exercises such as Qigong have reported promise in reducing symptoms. This study was designed to evaluate the feasibility and effect of Guolin Qigong on cancer-related fatigue and other symptoms in breast, lung and colorectal cancer survivors while exploring their perceptions and experiences of Guolin Qigong intervention.

**Methods::**

This is an open-label randomized controlled trial with 60 participants divided into 2 study groups in a 1:1 ratio. The intervention group will receive 12 weeks of Guolin Qigong intervention with a 4-week follow-up while control will receive usual care under waitlist. The primary outcome will be feasibility measured based on recruitment and retention rates, class attendance, home practice adherence, nature, and quantum of missing data as well as safety. The secondary subjective outcomes of fatigue, sleep quality and depression will be measured at Week-1 (baseline), Week-6 (mid-intervention), Week-12 (post-intervention), and Week-16 (4 weeks post-intervention) while an objective 24-hour urine cortisol will be measured at Week-1 (baseline) and Week-12 (post-intervention). We will conduct a semi-structured interview individually with participants within 3 months after Week-16 (4 weeks post-intervention) to obtain a more comprehensive view of practice adherence.

**Discussion::**

This is the first mixed-method study to investigate the feasibility and effect of Guolin Qigong on breast, lung, and colorectal cancer survivors to provide a comprehensive understanding of Guolin Qigong’s intervention impact and participants’ perspectives. The interdisciplinary collaboration between Western Medicine and Chinese Medicine expertise of this study ensures robust study design, enhanced participant care, rigorous data analysis, and meaningful interpretation of results. This innovative research contributes to the field of oncology and may guide future evidence-based mind-body interventions to improve cancer survivorship.

**Trial registration::**

This study has been registered with ANZCTR (ACTRN12622000688785p), was approved by Medical Research Ethic Committee of University Malaya Medical Centre (MREC ID NO: 2022323-11092) and recognized by Western Sydney University Human Research Ethics Committee (RH15124).

## Background

Cancer-related fatigue (CRF) has been increasingly recognized as an important symptom during and after treatment of cancer, impacting physical, mental, and emotional functions.^
1
^ CRF is a prevalent symptom among survivors of the most common types of cancer, including breast, lung, and colon cancer.^2,3^ It is a distressing symptom^
3
^ and one of the main reasons for the interruption of treatment or exacerbation of the disease.^
2
^ Between 74% and 90% of cancer survivors undergoing chemotherapy or radiotherapy^4
[Bibr bibr5-15347354241252698]-6^ experienced fatigue with adverse effect on other co-morbidity, quality of life, independent living, and work productivity.^3,7^ While fatigue is more prevalent within 6 months of receiving cancer treatment, cancer survivors including those who did not receive treatment continue to experience fatigue many years after treatment.^
5
^

Cancer diagnosis and its treatment also bring with it a host of physiological changes affecting various functions of the body including cortisol dysregulation associated with fatigue,^8
[Bibr bibr9-15347354241252698][Bibr bibr10-15347354241252698][Bibr bibr11-15347354241252698]-12^ sleep disorders,^8,13
[Bibr bibr14-15347354241252698]-15^ depression,^12,16^ anxiety, stress,^17,18^ functional disability,^
12
^ survival outcomes, and prognosis^13,18
[Bibr bibr19-15347354241252698][Bibr bibr20-15347354241252698]-21^ in cancer survivors.

The pathogenesis of CRF is still unclear, but might include proinflammatory cytokines, growth factors, circadian rhythm modulation, adrenal axis interruption, serotonin imbalance, afferent activation of the vagus nerve, and the production or use of abnormal adenosine triphosphate.^
22
^ Host factors not related to cancer and its treatment such as genetic, biological, psychosocial, and behavioral factor also play an important role in the development of CRF.^
23
^

CRF is also associated with various risk factors such as low performance status, undergoing chemoradiotherapy, insomnia, pain, neuroticism, depression and being female.^
24
^

It is further suggested that cancer-related fatigue is a composite of interacting responses to stress related to diagnosis and treatment, with the relationship of sleep disorders, depression, anemia, and inflammation featuring centrally for those under treatment as well as into the survivorship phase.^
25
^ CRF and a number of these factors and symptoms, including sleep disruption and emotional distress often co-occur as a symptom cluster,^26
[Bibr bibr27-15347354241252698]-28^ with some of these associations potentially linked to the underlying inflammatory biomarker changes such as cortisol level^
29
^ most associated with fatigue.^3,24,30^

Exploring symptom clusters is an important gap in symptom research to shed light on the common biological mechanisms^
31
^ and is gaining increased attention in the field of oncology in an attempt to improve the quality of life of patients diagnosed with cancer.^
32
^

Hence, there is a need to pay attention to the co-occurrences of fatigue, sleep disorder and depression as a symptom cluster in the evaluation and treatment of cancer survivors experiencing CRF.^3,26
[Bibr bibr27-15347354241252698]-28^

In spite of fatigue being the most common symptom reported by patients, they were least likely to report getting wanted help for it, perhaps due to the complexity of treating this common condition.^
5
^ Given the multifactorial nature of CRF which is still poorly understood, there is currently no “gold standard” treatment for CRF despite some approaches such as exercise, psychosocial interventions, and mind-body interventions being reported to yield beneficial effects in improving CRF.^
23
^

Emerging studies have shown that mind-body exercise such as Qigong can reduce fatigue, improve sleep, depression, anxiety, quality of life and cognitive changes associated with cancer as well as biomarkers of stress, cortisol level, inflammation and immune function in cancer survivors during and after treatment.^29,33
[Bibr bibr34-15347354241252698][Bibr bibr35-15347354241252698][Bibr bibr36-15347354241252698][Bibr bibr37-15347354241252698][Bibr bibr38-15347354241252698][Bibr bibr39-15347354241252698][Bibr bibr40-15347354241252698][Bibr bibr41-15347354241252698][Bibr bibr42-15347354241252698][Bibr bibr43-15347354241252698]-44^

The term “Qigong” is made up of 2 characters: Qi and Gong translated as the skill or practice to cultivate Qi. The concept of Qi, an inherent function and energizing essence of human being, is found in Traditional Chinese Medicine.^
45
^ Qi also refers to life force, vitality, or intelligence within a bio-electric body^46,47^ as well as the universe.^
48
^ There are a few thousand different forms of Qigong such as Tai Chi, BaDuanJin, Chan Chuang, Zhineng Qigong, and Guolin Qigong, all of which can be broadly classified into Chinese Medical Qigong, Daoist Qigong, Buddhist Qigong, Confucian Qigong, and martial arts Qigong. All forms of Qigong involve the recognition and cultivation of Qi to promote a balanced Qi and smooth flow of Qi in the body^
49
^ to enhance physical, psychological, and spiritual health through mind-body integration of specific movements, breathing techniques, and meditation.^
50
^ Mind-body integration of Qigong is also believed to promote health through the activation of neurohormonal pathways and other physiological mechanisms.^
51
^ Qigong offers several potential advantages when compared to modern medical therapy as it emphasizes a holistic approach with minimal adverse effects^40,52^ when practiced correctly after proper guidance. It is also known to improve neuropsychiatric conditions^
53
^ without the side effects of pharmaceutical drugs. More importantly, it promotes self-empowerment as it empowers individuals to take an active role in their health. Lastly, Qigong is more cost- effective compared to certain medical treatments as once learned, it can be practiced regularly to promote a healthy lifestyle without the need to incur additional expenses.

Among the many styles of Qigong is Guolin Qigong (GQ). This form of Qigong has been specifically adapted for cancer survivors by offering a moderate and adaptable exercise routine. It is a moderate walking exercise that integrates coordinated arm movements and trunk rotations, coupled with controlled breathing techniques. What sets it apart is its gentle nature, designed to be accommodating and adjustable. This adaptability is crucial, as it allows for modifications in speed, duration, and intensity, ensuring that it caters to the unique health conditions and needs of individual cancer survivors. The flexible approach of GQ prioritizes the well-being and comfort of each participant, making it a safe and beneficial practice for those navigating the complexities of cancer recovery. Therefore GQ is suitable for cancer survivors—especially advanced cancer patients who may be unable to engage in other forms of physical activity.^
54
^ A moderate-intensity walking exercise program was reported to be a feasible and effective intervention method for managing fatigue,^55,56^ anxiety, depression,^
57
^ and sleep in cancer survivors at different stages of cancer.^58
[Bibr bibr59-15347354241252698]-60^ GQ exercise training also facilitates the inhaling of oxygen which is important for the homeostasis of oxygen-carbon dioxide in controlling cancer and ultimately survival, as supported by a 10-year longitudinal cohort study of 122 lung and nasopharyngeal cancer patients which reported that improvements in End Tidal Breath Holding Time (ETBHT), alveolar O_2_ (aO_2_) pressure, and alveolar CO_2_ (aCO_2_) pressure capacity with GQ was associated with higher survival years, 5 years survival rate and survival probability.^
61
^ In the above-mentioned cohort study,^
61
^ GQ also demonstrated improvement in depression among cancer participants. Additionally, in breast cancer patients undergoing 5 to 6 weeks of radiotherapy, women with elevated depressive symptoms at the start of treatment showed significant enhancements in fatigue and QOL.^
50
^

However, the impact of GQ on CRF, often associated with sleep and depression^3,26
[Bibr bibr27-15347354241252698]-28^ and its correlation with cortisol levels has not been explored.

In addition to that, a qualitative study to evaluate the perception and acceptance of GQ is needed to explore the feasibility, adherence, and experience related to this complex intervention. It aims to understand the more subjective domains and identify potential factors for improving healthcare^
62
^ to address the multi-faceted needs of this population. Such research, however, has not been conducted yet.

Therefore, the purpose of this paper is to describe the protocol of a mixed-method study comprising,

A randomized-controlled trial to evaluate the feasibility of GQ training and its effect on CRF, sleep, depression, and cortisol levels in breast, lung and colon cancer survivors and,Semi-structured interview with study participants from the randomized- controlled trial to understand their perceptions and experiences of GQ to identify:
(a) other physiological and psychological benefits gained from the GQ intervention,(b) the barriers to GQ participation, adherence, and recommendations for improvement.

We hypothesized that

It is feasible for cancer survivor participants to engage in the GQ training and those who participated in the GQ training will experience positive impacts on CRF, sleep, depression, and cortisol level. Feasibility of this study is established at about 80% to 85% retention rate and 75% to 85% class attendance rate based on prior similar studies.^63
[Bibr bibr64-15347354241252698]-65^The semi-structured interview will identify a broader spectrum of benefits and barriers to participation and adherence to GQ training to provide valuable insights for program enhancement.

## Methods

### Study Design

#### Intervention/clinical trial

The primary objective of this study is to explore the feasibility of a GQ intervention in patients with various cancer types who experience CRF. This study includes the 3 most prevalent cancer types that is, breast, lung and colon cancers. This is a randomized-controlled trial that compares the GQ intervention group to a usual care waitlist control group receiving standard medical care allocated in a 1:1 ratio to evaluate the feasibility and effects of a 12-week GQ intervention on 60 eligible breast, lung, and colorectal cancer survivors’ fatigue, sleep quality, depression, and 24-hour urine cortisol change. Refer to Figure 1 for an overview of the study. This study protocol was developed based on the SPIRIT 2013 Statement (Standard Protocol Items: Recommendations for Interventional Trials) (Supplemental Material 1).^
66
^

**Figure 1. fig1-15347354241252698:**
[figure not shown]
Participant flow diagram.

#### Interview

We will use a qualitative descriptive design, with a semi-structured interview to collect in-depth information to enhance our understanding of the perceptions and experiences of GQ participation of cancer survivors based on purposive sampling until data saturation is reached.

The qualitative interview will be reported within the primary randomized feasibility trial according to the guidelines recommended in the CONSORT 2010 statement extension.^
67
^

### Study Setting

The trial is conducted at University Malaya Medical Centre (UMMC) in Kuala Lumpur, Malaysia. Participants are recruited by referrals from UMMC or online and print advertisements such as posting recruitment in UMMC, cancer support groups, GQ Association and GQ practice stations around Klang Valley, and social media platforms including X Corp (formerly known as Twitter) and Facebook.

### Recruitment

Recruitment started in October 2022. Upon first contact, the Researcher will screen potential breast, lung, or colon cancer survivors and provide information about the study to those who meet the eligibility criteria and indicate interest to participate. Thereafter a Physician/Oncologist Screening Form, Participant Information Sheet, and 2 copies of Participant Consent Form will be given, explained, and a separate date agreed for in-person enrollment.^
67
^

### Inclusion Criteria

(1) Age ≥ 18 years old;(2) *Cancer survivor diagnosed with breast, lung and colorectal cancer;(3) Able to read and answer questionnaires in English and/or Bahasa Malaysia language by oneself;(4) Suffering from moderate to severe fatigue as assessed by the simple fatigue scale; with severity score of 3 and above^
68
^;(5) Able to use smart phones and the WeChat or WhatsApp application;(6) Life expectancy of more than 3 months;(7) Able to give informed consent;(8) Available and willing to comply with the study requirements.

*A cancer survivor is defined as an individual diagnosed with cancer through the balance of life according to National Cancer Institute.^
69
^

Including cancer survivors throughout the continuum of survivorship in our sample inclusion criteria allows us to capture a comprehensive spectrum of experiences. From those newly diagnosed to long-term survivors, each stage brings unique perspectives on GQ participation and its impact. This approach ensures a thorough exploration of how GQ intervention intersects with varying phases of the cancer journey, providing a rich understanding of the diverse narratives and challenges encountered across this continuum.

### Exclusion Criteria

(1) Cardiopulmonary disease, nerve, muscle, or joint disease, or other malignant tumors affecting movement;(2) Mental illness or serious cognitive impairment and defects in language that significantly impairs communication;(3) Post-operative heart, cerebral vessel, or other serious complications;(4) Neurological degenerative disease (e.g. dementia), reduced cognitive; capacity in any way that would affect ability to understand trial procedures and give informed consent;(5) Patients who are not able to walk;(6) Other medical conditions which would preclude study intervention or make study participation unsafe such as severe chronic heart failure.

### Randomization and Blinding

After informed consent, participants will be randomly assigned to either the GQ or usual care waitlist control group at a 1:1 ratio with the random sequence generated by an online computerized randomization system using minimization method^70
[Bibr bibr71-15347354241252698]-72^ by an independent research assistant.

### Intervention

After being advised of group allocation, the study participant will be given a few days to decide on whether to proceed with enrollment. Incorporating a brief period for participants to reflect and opt-out after randomization supports ethical research practices, ensures ethical informed consent, reduces pressure, enhances retention, and respects participant autonomy in clinical trials or studies.

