### Study Assessments

The variables under consideration will encompass basic demographic data, primary outcomes, and secondary outcomes. Basic characteristics will be collected at baseline (Week-1).

Primary feasibility outcomes on adherence, attendance, and any adverse events will be recorded throughout the intervention period from Week-1 to Week-12 in the practice diary by the participants. Secondary patient-reported outcomes on fatigue, depression, and sleep will be measured at baseline (Week-1), mid-intervention (Week-6), post-intervention (Week-12), and 4 weeks after completion of intervention (Week-16). Urine samples (for urine cortisol test) to assess 24-hour urinary cortisol will be collected a day prior to enrollment date and post-intervention (Week-12). Primary feasibility outcomes and secondary patient-reported outcomes will be assessed by an independent research assistant to minimize bias. A summary of the planned data collection is shown in Figure 2.

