^ The PSQI was reported to be a stable measure of sleep quality with high test-retest reliability and construct validity.^79,80^

c. Depression—Centre for Epidemiologic Studies Depression (CES-D)

The CES-D is a short self-reported 20-item scale^
81
^ to be administered to measure depression symptoms at baseline, mid-intervention, post-intervention, and follow-up. The CES-D shows very high internal consistency and adequate test-retest repeatability.^
81
^ The score is the sum of all items, and the maximum score is 60. Scores ≥ 16 on the CES-D is considered as having “depressed symptoms.” The cut off score of 12 has been validated with DSM-III criteria for clinical depression.^81,82^

ii. Cortisol biomarker: 24-hour urine cortisol

Urine sample will be collected at baseline (Week-1) and post-intervention (Week- 12).^
83
^ Participants are briefed on the urine collection procedure during assessment and advised to obtain the 2.5 L urine collection container from any nearby BP Laboratories before baseline (Week-1) and post-intervention (Week-12). We use 24-hour urinary cortisol as a non-invasive, integrated measure of cortisol stress hormone activity that could be collected in participants’ home environments. Participants are instructed to collect all urine for 24 hours from 8:00am a day prior to baseline (Week-1) and post-intervention (Week-12) to 8:00am the next mornings and to send the urine sample collected to the nearest BP Laboratories the next morning itself. If the 2.5L collection container is completely full, subjects are advised to use a clean mineral water bottle to collect any specimen in excess of the 2.5 L collection. If subjects are unable to collect all urine for any reason, their samples will be deemed inadequate and no urinary cortisol data will be recorded for these subjects.

The 24-hour urine cortisol test provides a more accurate estimate of overall cortisol secretion^
84
^ to assess urinary-free cortisol (UFC) over a 24-hour period and provides an index of (unbound serum cortisol) the total amount of cortisol released by the adrenals. The 24-hour collection time reflects the amount of cortisol that is released over a complete circadian cycle, which is a physiologically meaningful unit of time. An integrated mean of cortisol levels over a 24-hour period is thought to provide a moderately stable measure of adrenocortical output.^
85

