## Data Analysis

### Quantitative Data

Data analysis will be conducted by an independent statistician. Data analysis will be by intention to treat using last observation carried forward (LOCF).^
93
^ The normality of the study data will be checked by examining the mean, median, skewness, and kurtosis including graphical representation of the box plot, normal Q-Q Plot or histogram. Continuous data will be summarized using descriptive statistics including the number of observations used in the calculation (*n*), mean, standard deviation (SD), minimum, median and maximum. Categorical data will be summarized as counts and percentages of each category. Between group comparison will be conducted using the t test, chi-square test, or Fisher exact test, as appropriate. We will report the results for two-sided 5% tests for the primary trial outcome. We will use generalized linear mixed model (GLMM). The outcomes of the model will be BFI, PSQI, CES-D scores, and 24-hour urine cortisol test results. Models will include the treatment group as a fixed effect, with time as a random effect to account for the repeated measurements. Analyses will be conducted to identify the baseline characteristics of the participants who may benefit most from the intervention. Model assumptions will be checked and appropriate adjustments to the analysis will be made where necessary. STATA^®^ software version 17.1 (2021; Stata Corporation, College Station, TX, USA) will be used for all analyses. Cohen’s D will be calculated as the absolute differences between the mean change in the variable divided by pooled variance of the change.

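### Participants learn their arm before deciding whether to enrol, and probably before baseline, so refusal can depend on the arm they drew

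*Protocol article*

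**What the plan says.** The section Randomization and Blinding fixes the first steps: "After informed consent, participants will be randomly assigned to either the GQ or usual care waitlist control group." The Intervention section then adds: "After being advised of group allocation, the study participant will be given a few days to decide on whether to proceed with enrollment." It describes this openly as a chance to leave after randomisation and defends it on the ground that it "ensures ethical informed consent, reduces pressure, enhances retention, and respects participant autonomy."

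Two sections date the baseline urine collection. Study Assessments says that samples "will be collected a day prior to enrollment date and post-intervention (Week-12". The section on patient-reported outcomes and the cortisol biomarker tells participants to "collect all urine for 24 hours from 8:00am a day prior to baseline (Week-1) and post-intervention (Week-12". The questionnaires share that time point: "Secondary patient-reported outcomes on fatigue, depression, and sleep will be measured at baseline (Week-1".

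For the analysis, the Quantitative Data section says: "Data analysis will be by intention to treat using last observation carried forward (LOCF". It also names a mixed model for the fatigue, sleep, depression and cortisol outcomes, and a Cohen's D built on mean change. Data Collection says that withdrawals after randomisation, whenever they happen, are recorded with reasons. Retention is one of the primary feasibility measures, and the hypothesis at the end of the Background sets its mark at about 80% to 85%.

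**The concern.** A reflection period normally comes before randomisation. Here it comes after the participant knows the result. One arm gets a supervised class straight away. The other waits until after Week 16 and is asked to keep away from other Qigong in the meantime. People recruited partly through Qigong associations and practice stations may well respond differently to those two offers. Refusal that depends on the arm is selection after randomisation, and it can make the groups differ in ways that randomisation was meant to prevent.

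Three things are at stake:

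- whether the analysed groups are still the randomised groups;
- whether the self-reported baseline scores are free of reactions to the allocation;
- whether the retention rate, which decides feasibility, describes everyone randomised or only those who accepted their arm.

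**Working it through.** The plan gives no opt-out rate, so there is no figure of its own to reproduce on this point. The check has two parts: the order of events, then the arithmetic of the denominator.

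**Order of events**

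1. Consent, then randomisation (Randomization and Blinding).
2. The arm is disclosed, then a few days pass before the participant decides whether to enrol (Intervention).
3. Baseline urine is collected the day before the enrolment date (Study Assessments).
4. The same collection is placed the day before baseline, Week-1 (cortisol biomarker section).
5. Steps 3 and 4 together make the enrolment date and baseline the same day. By step 2, that day follows disclosure.
6. The fatigue, sleep and depression questionnaires are taken at Week-1, so they follow disclosure too.

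**Consequence for the analysis set.** On this order, a person who opts out has no Week-1 questionnaire or cortisol value and none later. LOCF has nothing to carry forward, and the mixed model has no outcome record for that person.

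**Consequence for self-reported change.** Let disclosure shift the reported baseline by b₁ in the Qigong arm and b₀ in the waitlist arm, with later scores unaffected. The between-arm difference in mean change then moves by −(b₁ − b₀). The Cohen's D numerator is that difference, so any unequal shift enters it in full. The documents give nothing from which to estimate b₁ or b₀, and the direction could go either way.

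**Consequence for retention.** If the rate is counted from enrolment:

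retention among randomised = retention among enrolled × (1 − opt-out share)

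The opt-out shares below are assumed. The 80% and 85% are the two ends of the plan's mark.

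| Opt-out share (assumed) | 80% of enrolled becomes | 85% of enrolled becomes |
|---|---|---|
| 0% | 80.0% | 85.0% |
| 5% | 76.0% | 80.8% |
| 10% | 72.0% | 76.5% |
| 15% | 68.0% | 72.3% |
| 20% | 64.0% | 68.0% |

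The share that takes 85% of the enrolled down to 80% of the randomised is 1 − 0.80/0.85 = 0.0588, or 5.9%. With 60 randomised that is 0.0588 × 60 = 3.5 people.

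An example with assumed counts: 60 are randomised, 6 opt out and 8 drop out later, which leaves 46. From enrolment, retention is 46/54 = 85.2%. From randomisation it is 46/60 = 76.7%. If 5 of the 6 opt-outs were on the waitlist, that arm would lose 5/30 = 16.7% by choice, against 1/30 = 3.3% in the Qigong arm.

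**The case against.** The strongest objection concerns the word enrolment. The Recruitment section speaks of agreeing a date for in-person enrolment at first contact, before randomisation is described. If Study Assessments means that visit, the urine sample would precede allocation. Figures 1 and 2, which might settle the order, are not shown. This stands as a real ambiguity. It makes baseline after disclosure an inference, though the better one, because the Intervention section expressly puts the enrolment decision after allocation.

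A reader might infer that the plan removes opt-outs from the ITT set and from the retention rate. It does not say so. It states intention to treat, it records withdrawals at any point after randomisation, and it gives no retention denominator. Such definitions are commonly left to a full protocol or SAP, so their absence from an article is not itself a fault. The claim that the opt-out helps retention fits most easily with opt-outs not being counted as lost, but it is one item in a general rationale and proves nothing.

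A reader might also infer that people who opt out leave no data at all. That is too absolute: eligibility requires a fatigue severity score of 3 or more, so a screening fatigue score exists. The plan does not say that it would serve as a baseline.

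Nor does the concern about reporting reach every outcome. Urinary cortisol is a laboratory assay, so knowing the arm does not colour it as it can colour a questionnaire. Finally, the efficacy outcomes are secondary, and the Limitations section already admits that participants are unblinded. It does not mention opt-out after disclosure or the timing of baseline, and an open-label trial can still protect both.

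**Conclusion.** The point holds. That participants may refuse after learning their arm is stated outright, and this alone allows selection by arm after randomisation. The rest is conditional:

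- If baseline coincides with enrolment, as the text most naturally reads, the named LOCF and mixed-model analysis has no Week-1 value for those who opt out. The analysed set would be those who accepted their arm, and the three self-reported baselines would be given with the arm known.
- If retention is counted from enrolment, it is overstated. An opt-out share of about 5.9% is enough to separate 85% from 80%, the two ends of the plan's own mark.

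The actual size of either bias cannot be calculated, because the article gives no opt-out rate and no split by arm. The shares of 0% to 20% and the example counts are assumptions. If baseline is in fact taken before disclosure, the concern about self-reported baselines falls away and opt-outs would have a first value. The arm-dependent refusal and the choice of denominator would remain.

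**What to change.** - Place the reflection period between consent and randomisation. This serves the same ethical aim, and the right to withdraw at any time is unchanged.
- Complete the baseline questionnaires and the baseline urine collection before allocation is disclosed, and use one meaning of enrolment throughout.
- State that the ITT set and the retention denominator are all randomised participants, and report retention by arm.
- For people already randomised (recruitment began in October 2022), report post-allocation opt-outs by arm and count them as not retained. Re-ordering the steps can help only later participants.

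The cost is a short amendment, a few baseline assessments on people who then decline before randomisation, and possibly a lower reported retention rate.
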